#### Secondary variable analyses

To determine which factors are associated with clinical-radiological success in the short term, a multivariate logistic regression will be carried out. The variables of age and sex, and factors predicting the location of the disease, treatments received, size, and characteristics of the collection, previous ASA, etc. will be taken. In addition, the appearance of clinical recurrence will be considered by means of an analysis of Kaplan-Meier survival. The factors associated with clinical recurrence will be explored through a multivariate Cox proportional risk model and adjustment variables will also be taken.

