## Background

The Atlanta classification of pancreatic-fluid collection establishes that walled-off necrosis (WON) consists of a variable amount of necrotic tissue within a reactive-tissue wall. This derives from the encapsulation of acute necrotic collections. Imaging tests reveal a well-defined wall surrounding the collection, the formation of which typically occurs at about 4 week from the origin of the acute or chronic pancreatitis. The presence of more necrosis worsens the prognosis; mortality in patients with necrotizing pancreatitis is as high as 15%, and it can reach 30% in patients with infected necrosis [1, 2]. In case of symptomatic WON, drainage is considered, and in the last two decades minimally invasive approaches (surgical or endoscopic) have enjoyed increased acceptance in the management of necrotic collections over open surgical necrosectomy, with fewer adverse events (AEs) and less long-term morbidity. Recent trials have shown that endoscopic approaches offer better clinical outcomes, with improvement in quality of life and lower costs [3–6].

In the last few decade, endoscopic techniques, such as the use of endoscopic ultrasound-guided transmural drainage, have been increasingly used as a first-line option for the treatment of symptomatic WON [5, 7]. To date, plastic stents (such as double plastic stents) have been become the mainstay of endoscopic therapy for WON, until the introduction of lumen-apposing metal stents (LAMS) [8–10]. There is the hypothesis that the large diameter of LAMS improves the drainage of WON with respect to plastic stents (7–10 Fr) and carries less time-consuming interventions, with a smaller number of endoscopic procedures to achieve final success. Regarding safety, the risk of leakage, perforation, or migration would theoretically be reduced using the specific stent design of LAMS. However, LAMS are more expensive, and their safety is controversial, with a significantly higher rate of AEs, such as bleeding, compared with plastic stents [11–14] (Table 1).

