#### Follow-up

Patients will be assessed (visit, telephone call) on days 1 and 7, at 4, 8, and 16 weeks, and at 6, 8, and 12 months by personnel participating in the study, with the aim of obtaining information regarding signs and symptoms pointing to possible stent obstruction or migration, recurrence, or other AEs.

Any instances of death during the follow-up will be investigated to rule out any possible relation to the endoscopic procedure. Such occurrences will also be recorded in the CRF.

If there is clinical suspicion of obstruction or migration of the stent, an upper endoscopy will be carried out. Based on the findings of this procedure, the problem will be resolved in accordance with the directives of the intervening endoscopist. Any additional procedure or endoscopic intervention will be duly documented.

Complications will be handled and treated in accordance with the directives of the patient’s medical team. All additional tests and interventions will be duly documented.

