### Definitions

The term WON is in accordance with the literature (latest revision of Atlanta, Banks PA et al. Gut 2013) [1]. At least two imaging tests will be required (CTMD, MRI, EUS) prior to the transmural drainage, the results of which must be in agreement on the classification of the collection as WON.

Technical success is defined as the correct release of the stent at both ends, with observed drainage of the liquid.

Clinical success is defined as the significant reduction of the collection along with clinical resolution.

Recurrence is defined as a symptomatic pancreatic collection diagnosed with imaging test during the follow-up of prior procedure with initial clinical success.

AEs are defined as undesirable situations suffered by patients during the study, whether related or not to the EUS-guided transmural drainage with a stent (plastic or metal). All AEs referred by patients or observed by the medical team will be duly documented. All serious AEs will be detailed, and the study promoter/principal investigator will be notified within 7 days. In the event of a death, notification will be made within 24 h. AEs will be recorded in both the clinical history of the patient and the CRF, with appropriate medical terminology. Whenever possible, the diagnosis rather than the symptoms will be recorded. These guidelines are to be followed from the time of the signing of informed consent until 30 days after the final visit in the study calendar. AEs will be classified as mild, moderate, serious, or fatal, in accordance with the nomenclature for AEs in endoscopy (ASGE Workshops 2010, Cotton GIE 2010; 71:446–54). The determination as to whether an AE is related to the EUS-guided transmural drainage with stent (plastic or metal) will be made by the patient’s medical team, the local investigator, and the principal investigator of the study.

In Additional file 2 is included information about AE definitions and MEDDEV guidelines. “Research product security surveillance” section, according to the definitions set out in the MEDDEV 2.7/3 guidelines (rev 3, May 2015) “Guidelines on medical devices: Clinical investigations: Serious adverse event reporting under Directives 90/385/EECC and 93/42/EEC” (Additional file 2).

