### Other considerations

#### Rescue

Depending on the initial endoscopic treatment carried out, a cross-over rescue treatment may be considered when the initial protocol treatment fails. For the plastic treatment group ➔ metal stent (LAMS); for the metal treatment group ➔ plastic stent. Another accepted rescue technique (only in cases of initial treatment failure) in the branch of metal stent: insertion of coaxial plastic pigtail within a LAMS.

In all these cases, the follow-up of the patients will be maintained until the end of the study according to protocol. Alternatively, if a cross-over treatment or technical variant is not possible, percutaneous surgical or radiological treatment will be offered.

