#### Withdrawal

Any AE or other clinical condition of the patient which, at the clinician’s discretion, warrants withdrawal of the patient from the study; pregnancy; or expressed wishes of the patient. Withdrawal from treatment will not mean suspension of the study, given that follow-up will be maintained until the end of the study in accordance with the protocol.

The need for surgical intervention for: in these cases, patient follow-up will be ended.

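### Kaplan-Meier for recurrence can only censor deaths, so it somewhat overstates the actual 12-month risk; a cumulative incidence with death as a competing event is the better estimate

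*Protocol article*

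**What the plan says.** Under Secondary variable analyses the protocol article names two methods for recurrence. For its occurrence, "the appearance of clinical recurrence will be considered by means of an analysis of Kaplan-Meier survival". For its predictors, "The factors associated with clinical recurrence will be explored through a multivariate Cox proportional risk model". No competing-risk method is named.

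The Definitions section restricts the outcome: "Recurrence is defined as a symptomatic pancreatic collection diagnosed with imaging test during the follow-up of prior procedure with initial clinical success". The Follow-up section sets assessments on days 1 and 7, then "at 4, 8, and 16 weeks, and at 6, 8, and 12 months", and provides for deaths: "Any instances of death during the follow-up will be investigated to rule out any possible relation to the endoscopic procedure". Their role in the recurrence analysis is not stated.

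On surgery, the Withdrawal section has a sentence that breaks off before naming the reason for surgery and then says "in these cases, patient follow-up will be ended". The Rescue section, after describing cross-over and coaxial rescue, says "In all these cases, the follow-up of the patients will be maintained until the end of the study according to protocol". Its next sentence offers surgical or radiological treatment as the alternative when those options are not possible.

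**The concern.** A patient who dies can no longer have a recurrence. Kaplan-Meier with recurrence as the event treats that patient as censored, that is, as someone who would have gone on to recur at the same rate as those still observed. The complement of the curve then describes recurrence in a population in which nobody dies. It does not describe the share of successfully drained patients who recur within 12 months, which is the figure a clinician would quote from the trial.

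At stake is the recurrence percentage in each arm. If deaths after success differ between arms, the contrast between the two percentages is affected as well. Ending follow-up at surgery raises a related question, because it makes surgery a censoring event that may not be independent of the risk of recurrence.

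**Working it through.** **Figures in the plan.** The article gives no recurrence rate and no rate of death or surgery after success, so there is no recurrence figure to reproduce. The only planning figures needed are those that fix how many patients are at risk (Sample-size calculation): success of 0.75 with LAMS and 0.50 with plastic, 57 per arm. The 57 can be checked with the pooled two-proportion formula, two-sided 5%, 80% power:

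(1.960 × √(2 × 0.625 × 0.375) + 0.842 × √(0.75 × 0.25 + 0.50 × 0.50))² / 0.25² = 57.67

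This rounds up to 58, within one patient of the stated 57, before any allowance for loss.

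**Patients at risk of recurrence.** Taking initial clinical success to be success at 4 weeks (an assumption): 0.75 × 57 ≈ 43 with LAMS and 0.50 × 57 = 28.5 with plastic.

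**Direction.** Let λr and λd be the hazards of recurrence and of death. The cumulative incidence adds up λr multiplied by the probability of being alive and free of recurrence. The complement of Kaplan-Meier adds up λr multiplied by the Kaplan-Meier probability of being free of recurrence, which takes no account of deaths and so is never the smaller of the two. Hence 1 minus Kaplan-Meier is never below the cumulative incidence, and it is above it when deaths occur among patients still at risk.

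**Size.** Assume constant hazards. R is 1 minus Kaplan-Meier for recurrence at 12 months and D is the net risk of death over the same time. Both are assumed.

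λr = −ln(1 − R), λd = −ln(1 − D), CIF = λr / (λr + λd) × (1 − exp(−(λr + λd)))

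Example, R = 15% and D = 5%: λr = 0.1625, λd = 0.0513, and 1 − 0.85 × 0.95 = 0.1925. CIF = 0.1625 / 0.2138 × 0.1925 = 14.6%.

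| D (R = 15%) | CIF | Overstatement, points | Relative |
|---|---|---|---|
| 2% | 14.85% | 0.15 | 1.0% |
| 5% | 14.6% | 0.4 | 2.5% |
| 10% | 14.3% | 0.7 | 5.2% |
| 15% | 13.9% | 1.1 | 8.1% |
| 30% | 12.7% | 2.3 | 18.3% |

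Over a wider grid (R from 5% to 30%, D from 2% to 30%) the overstatement runs from 0.05 to 4.5 points.

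**Against sampling error.** For a recurrence of 15% the standard error is √(0.15 × 0.85 / 43) = 5.4 points with 43 patients and √(0.15 × 0.85 / 29) = 6.6 points with 29. At D = 15% the overstatement amounts to 43 × 0.0112 ≈ 0.5 of a patient.

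**Between arms.** With equal recurrence hazards (R = 15% in both arms) and D of 5% against 15%, the overstatement is 0.4 against 1.1 points, a difference of about 0.8 before rounding. Without equal hazards the order can reverse on the absolute scale: R = 30% with D = 10% gives 1.4 points, while R = 10% with D = 15% gives 0.8. On the relative scale the second arm still has the larger overstatement (8.2% against 5.0%).

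**The case against.** The case against acting has several parts.

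- **The effect is small.** At the lower death risks it is a fraction of a point, on a secondary outcome with few patients at risk. This stands, and it limits the weight of the point.
- **Nothing says that deaths are censored, and the SAP may settle it.** The article does not write out the censoring rule, and crude percentages by arm would also be available from the descriptive analysis. But the method is stated, and plain Kaplan-Meier for recurrence cannot handle a death in any other way. The Statistical analysis plan section says that the SAP will contain the analyses described together with others, so this choice carries forward.
- **The two curves answer different questions.** With equal recurrence hazards, equal Kaplan-Meier curves are a correct report of that equality, and a lower cumulative incidence in the arm with more deaths could be mistaken for benefit. This stands, and it is why the competing events must be shown beside the curve.

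Some stronger readings are tempting, but the article does not support them.

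- A reader might take the mortality quoted in the Background, "mortality in patients with necrotizing pancreatitis is as high as 15%, and it can reach 30% in patients with infected necrosis", as the competing risk. Those figures describe the disease as a whole, whereas recurrence is counted only after initial success, which leaves out earlier deaths. D = 30% would mean about 0.30 × 43 ≈ 13 deaths among 43 successfully drained patients if none recurred first.
- A reader might infer that the arm with more deaths always has the larger bias. That needs equal recurrence hazards or a relative scale.
- A reader might infer that the trial expects deaths or surgery after success to differ by arm. The article expects different 4-week success and reports more adverse events, such as bleeding, with LAMS. It states no expectation about death or surgery after success.
- A reader might treat surgery like death. A collection can still form after surgery. If patients sent to surgery are at higher risk, ending their follow-up could understate recurrence, so the direction is uncertain.

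**Conclusion.** The point holds for death, in a limited form. The stated method overstates the actual 12-month risk of recurrence whenever patients die after initial success. The direction is certain. The size rests on assumed rates: 0.15 to 1.1 points for a Kaplan-Meier recurrence of 15% and a competing death risk of 2% to 15% under constant hazards, against a standard error of about 5 to 7 points. A difference in bias between arms arises if deaths differ, subject to the condition on hazards or scale given above.

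For surgery, the conclusion is only that ending follow-up may be informative censoring, of unknown direction, and that the relevant sentences do not fit together clearly. The primary analysis and the sample size are not affected, and the Cox model remains usable as a cause-specific model. The reason to act is that the bias is systematic and its correction nearly free.

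**What to change.** 1. Report the Aalen-Johansen cumulative incidence of recurrence by arm, with 95% CI, among patients with initial clinical success and with death as a competing event.
2. Show deaths and surgery by arm beside it, so that a lower recurrence caused by more deaths is not read as benefit.
3. Keep the Cox model and label its results as cause-specific hazard ratios.
4. State how surgery enters the analysis: as a competing event, or as censoring with a sensitivity analysis.
5. Complete the surgery sentence in Withdrawal and reconcile it with the statement on continued follow-up in Rescue.

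Cost: a few lines of SAP wording and a standard software routine. Deaths and additional interventions are already to be recorded in the CRF, so the only data needed are their dates. The downside is one more curve and table per arm.

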#### Subgroup analysis

The main analysis will also be carried out in the following subgroups:

ASA patients I–II vs. II–IV.

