### Randomization and masking

Patients will be enrolled in this trial by gastroenterologists, surgeons, and endoscopists who will evaluate the cases in the inpatient wards or in the outpatient consultation areas. The participants will be randomized with a random-number table generated by an online platform.

A code list will be generated by randomization with a 1:1 randomization ratio, by blocks, stratified by centers and by American Society of Anesthesiologists’ classification (ASA) score. Each individual will be assigned a randomization code along with the treatment that corresponds. Once the patient meets the eligibility criteria and has provided informed consent, we will proceed to the allocation of each participant centrally, ensuring allocation concealment, and based on the randomization list. To prevent different subject recruitment rates at the various hospitals from interfering with the development of the study, the entire population will be randomized in blocks of four between the two treatment possibilities.

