### Sample-size calculation

The sample-size calculation is based on the primary hypothesis of detecting statistically significant differences in the percentage of clinical success in the LAMS and plastic-stents groups at 4 weeks after the intervention. Published data suggest that the clinical success rate at 4 weeks in the LAMS group is expected to be 0.75 and in the plastic-stent group it is expected to be 0.5. Fifty-seven patients will be recruited in each group to reject the null hypothesis that the proportion of clinical success in the LAMS group is equal to that of the plastic group with an 80% power. The type-I error associated with this test will be 5%. To evaluate the hypothesis, the chi-square test or Fisher’s exact test will be used depending on of the application criteria. For the calculation, a planned interim analysis will be made for half of the recruitment using O’Brien-Fleming’s type-I error expense function and a global loss rate of 5%. http://www.stat.ubc.ca/~rollin/stats/ssize/b2.html

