### Statistical analysis

All study variables will be presented for stent groups and in total, using descriptive statistics consistent with the nature of the variable. The continuous variables will be described indicating the number of non-missing observations, the mean, the standard deviation, the minimum, the first quartile, the median, the third quartile, and the maximum. Categorical variables will be described indicating the number of non-missing observations and the percentages of the different categories by column.

Main analysis: main outcome is the percentage of patients’ radiological (morphological) success between transmural drainage of the collection, measured at 4 weeks from intervention. The null hypothesis suggests that there are no differences between the proportions of the intervention group and the control group.

The level of statistical significance has been set at 5%. To test the hypothesis, use the chi-square test or Fisher’s exact test depending on the application criteria will be used. To quantify the magnitude of the difference, the relative risk of success will be estimated, in the metal-stent group with respect to the plastic-stent group and its confidence interval will be calculated at 95%.

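### The only stated subgroup analysis puts ASA II in both groups as printed, and repeating the main test in each group does not show whether the stent effect differs by ASA

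*Protocol article*

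**What the plan says.** The Subgroup analysis section of the protocol article is a single item. It states that "The main analysis will also be carried out in the following subgroups" and then gives one pair of groups: "ASA patients I–II vs. II–IV".

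The Statistical analysis section defines the main analysis. It is a chi-square or Fisher's exact test at the 5% level of the null hypothesis that "there are no differences between the proportions of the intervention group and the control group". In addition, "the relative risk of success will be estimated, in the metal-stent group with respect to the plastic-stent group", with a 95% confidence interval.

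ASA appears in two other places, without categories in either:
- Randomization and masking says that allocation is "by blocks, stratified by centers and by American Society of Anesthesiologists" score.
- Secondary variable analyses lists ASA among the candidate factors in a logistic model for short-term success. No interaction between stent and ASA is mentioned.

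The Statistical analysis plan section says that the later plan will contain every analysis described in the protocol plus others, that it will be finalised before the database closes, and that it will not change after that.

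**The concern.** There are two separate problems.

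**The groups.** A subgroup comparison needs groups that do not share patients. As printed, every ASA II patient is on both sides. The likely intention is I–II against III–IV. A slip in the first group, with I against II–IV intended, cannot be excluded from the text. These two readings place all ASA II patients in different groups. If the choice is made only once results are known, the subgroup is no longer pre-specified.

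**The method.** The wording sets one ASA group against the other, which suggests interest in whether the stents compare differently in fitter and sicker patients. What is specified is the stent comparison within each group. If one result is significant and the other is not, that is easily read as a difference in effect, but it is not evidence of one. With 114 patients in all, such a split result is likely by chance alone.

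**Working it through.** **Inputs.** From Sample-size calculation: success 0.75 with LAMS and 0.50 with plastic, 57 patients per group, 80% power, 5% type-I error, 5% losses. The error rate is read as two-sided because the null is one of equality. The protocol gives no ASA distribution, so every ASA share below is an assumption, shown over a range.

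**1. The plan's own figure.** The unpooled two-proportion formula gives n = (1.960 + 0.842)² × (0.75×0.25 + 0.50×0.50) / 0.25² = 7.849 × 0.4375 / 0.0625 = 54.9, so 55 per arm. With 5% losses, 55/0.95 = 57.9, so 58. The pooled formula gives 58 before losses. Both are within one patient of 57. Pooled-formula power at 57 per arm is 79.5%, so the planning assumptions can be carried into the subgroups.

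**2. Power within one disjoint group.** An even split gives 57/2 = 28.5, taken as 28 per arm.
- Standard error under the null: √(2 × 0.625 × 0.375 / 28) = 0.1294.
- Standard error under the alternative: √(0.4375 / 28) = 0.1250.
- Power = Φ[(0.25 − 1.960 × 0.1294) / 0.1250] = Φ(−0.03) = 48.9%.

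**3. Chance of a split result when the effect is the same in both groups.** The groups are disjoint, so the tests are independent.
- Exactly one significant: 2 × 0.489 × 0.511 = 50%.
- Both significant: 0.489² = 24%.
- Neither significant: 0.511² = 26%.

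With uneven splits (ASA I–II share 30% to 70%), power within a group ranges from 32% to 64%. The chance of exactly one significant result is 50% to 55%. At 30/70, for example: 0.321 × 0.360 + 0.640 × 0.679 = 55%.

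**4. What the overlap would do if the text were applied literally.** The two group sizes would add up to 114 plus the number of ASA II patients. For an ASA II share of 25% to 60%, that is about 142 to 182. The correlation between the two estimates is about s₂ / √[(s₁ + s₂)(s₂ + s₃)], where s₁, s₂ and s₃ are the shares of ASA I, II and III–IV. Over the mixes tried it is 0.41 to 0.76.

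Suppose the true effect were 25 points in I–II and zero in III–IV. The II–IV group would then show 25 × s₂ / (s₂ + s₃) points.
- Shares 10/30/60%: 25 × 0.30/0.90 = 8.3 points, so the apparent contrast is 16.7.
- Shares 10/60/30%: 25 × 0.60/0.90 = 16.7 points, so the apparent contrast is 8.3.

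A true contrast of 25 points would therefore appear as about 8 to 17.

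**5. Power of an interaction test.** Take the same pattern (25 points in I–II, zero in III–IV), a plastic success rate of 0.50 and an even split of 28.5 per arm.
- Risk difference: variance = (0.4375 + 0.50)/28.5 = 0.0329, standard error 0.181; Φ(0.25/0.181 − 1.960) = 28%.
- Log relative risk: variance = (0.333 + 1 + 2)/28.5 = 0.117, standard error 0.342; Φ(0.405/0.342 − 1.960) = 22%.

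For ASA I–II shares of 40% to 70%, the ranges are 24% to 28% and 18% to 22%.

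**The case against.** The strongest reply is that this is a one-character slip in a condensed article. The contrast is worded as two opposing groups, and I–II against III–IV is the natural reading. A reader might infer from the printed text that ASA II patients will in fact be analysed twice. The document does not support that as a prediction, because it happens only if the line is applied literally. What stands is that the definition is wrong as written, that nothing elsewhere corrects it, and that the protocol carries its described analyses into the later plan.

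Second, an interaction test may well be in the statistical analysis plan, which is not shown. That is fair, and its absence from the article does not show that no such test will be done. The point concerns the method that the protocol does state, which is a separate analysis within each group.

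Third, the protocol nowhere says that two p-values will be compared, and relative risks with confidence intervals are already planned in each group. Both observations are correct. The estimates can stay. What is missing from the stated method is a basis for saying that they differ.

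Fourth, low subgroup power is ordinary and not an error in itself, and the interaction test is weak as well. This also stands. The figures in steps 2 and 3 describe disjoint groups, so they illustrate the problem with separate tests and do not measure the overlap.

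Finally, because ASA is a randomisation factor, a reader might infer that the unclear cut disturbs the primary analysis. It does not. The main test is an unstratified chi-square or Fisher's exact test, and nothing ties the subgroup cut to it.

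**Conclusion.** The point holds as a minor one. The printed ASA groups overlap and the document does not settle the intended cut. Repeating the main test in each group does not test whether the stent effect depends on ASA. With an even split and the same 0.75 against 0.50 effect in both groups, each test has about 49% power and exactly one is significant about half the time. For ASA I–II shares of 30% to 70%, that chance is 50% to 55%. These figures rest on assumed ASA shares and the normal approximation. The 8-to-17-point contrast in place of 25 applies only if the overlapping groups are used literally. The primary comparison and the sample size are not affected.

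**What to change.** Before the database closes:

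1. State mutually exclusive ASA groups, for example I–II against III–IV if that was intended. Make them compatible with the ASA levels used to stratify randomisation, and state those levels in the same place.
2. Base any statement that the stent effect differs by ASA on one stent-by-ASA interaction test, not on which group reaches 5%.
3. Keep each group's relative risk and 95% confidence interval, and label the whole subgroup analysis exploratory.

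The cost is a line or two of text and no extra data. The one drawback is that the interaction test has low power (about 18% to 28% in the scenario above), so a non-significant result must not be reported as evidence that the effect is the same in both groups.
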